## Methods

### Overview

This study aims to discover the characteristics of the e-psychonaut population and the effects of the NPS they use, with a longitudinal design and no control group. The study is conducted online, recruiting participants using an innovative and specifically developed platform as part of the study project: Global Research and Analysis of New Substances Project (GRASP).

The study has been designed and will be reported using the Checklist for Reporting Results of Internet E-Surveys [28] and the STROBE (Strengthening the Reporting of Observational Studies in Epidemiology) statement checklist for observational studies [29], with the support of the SPIRIT (Standard Protocol Items: Recommendations for Interventional Trials) statement checklist of 2013 [30].

The study protocol was submitted in October 2018 and was approved by the Clinical Research Ethics Committee (Parc de Salut Mar, Barcelona, Spain, ref. 2018/8283/I) in January 2019. The study was conducted according to the Declaration of Helsinki recommendations and the emerging recommendations for online research on sensible topics [21,25]. All data collected online on the participants were encrypted according to the European and Spanish data protection regulations (2016/679 European Parliament and 27/4/16 reglamento general de protección de datos [general law about data protection] Spanish Royal Decree).

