The first mandatory step was to fill a sociodemographic and drug use history questionnaire (Q1). This questionnaire was available to each participant through a participant-specific link, which was sent by email once they were accepted. After that, participants were asked to fill the sample submission questionnaire (Q2), where information about the sample they intended to consume was asked. This questionnaire was then reviewed by the principal investigator and approved if the substance met the study criteria of being a new psychoactive substance. The samples that did not meet the inclusion criteria were not accepted, and the participant was notified by email. The sample submission questionnaire (Q2) was available to all accepted participants as a link on the platform. All the questionnaire answers were reviewed weekly by a member of the research team to communicate to the participant the acceptance of the sample and to mark them as valid or invalid data for later analysis.

If the sample was approved, the participant received a specifically generated sample code with the instructions to send a small amount of the sample (approximately 30 mg, usually below the psychoactive threshold) via traditional mail to the laboratory at the IMIM. The sample was analyzed there, and the result was sent back to the user, along with harm reduction advice when appropriate.

Meanwhile, the users could consume the substance whenever they decided, as the study was intended to be observational. However, most of the participants waited until they had the result of the laboratory analysis to proceed with the self-administration trial. The self-administration trial started with the users filling the drug effect baseline questionnaire (Q3a), and then, they consumed the reported substance and filled the drug effect questionnaire (Q3b) 24 hours after filling the baseline questionnaire (Q3a). The links to these questionnaires were available for all participants in the forum, and the veracity of the information was ensured by asking information only available to each participant, such as the sample code of the reported sample.

Study recruitment began in August 2019 and is still ongoing. In August 2020, the first participant concluded the 1-year follow-up.

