Q0, screening questionnaire [53]: contained a total of 37 questionsQ1, sociodemographic questionnaire [54]: contained a maximum of 351 questions, with an expected average per participant of 50, due to adaptive questioning and questionnaire logicQ2, sample submission questionnaire [55]: contained a total of 21 questionsQ3a, baseline drug effect questionnaire [56]: contained a total of 12 questionsQ3b, drug effect questionnaire given 24 hours after drug administration [57]: contained a total of 39 questionsQ4, 1-year follow-up questionnaire [58]: contained a maximum of 351 questions, with an expected average per participant of 50, due to adaptive questioning and questionnaire logic.

The number of pages and items on each page were optimized automatically by *Qualtrics* software and varied according to the screen size used to answer. The possibility to answer the questionnaires comfortably from the smartphone was assessed as an essential by the research team.

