As it is an exploratory study, the data analysis procedures will be mainly descriptive statistics, to maximize an adequate visualization of the data collected within the minimum space. In addition, as there is no control group, statistical tests will be limited to potential comparisons to assess bias on the results, such as comparing data from participants who complete the study with participants who drop out or are excluded. However, no statistical corrections will be applied to adjust the representativeness of the sample, as this validation will be done by comparing the sociodemographics of the study sample with the characteristics of the population of psychonauts widely reported in the literature. Statistical tests might also be used to compare information from the initial questionnaire Q1 and the data from the follow-up questionnaire Q4. The nonparametric Wilcoxon signed-rank analysis will be used to perform a mean comparison of the quantitative data and the chi-square test for qualitative data. In addition, factor analysis will be attempted to study the relationship between all the visual analog scales used to assess the subjective drug effects.

The data analysis will focus on the outcomes of the participants who completed the study. Data entries containing evident errors or inconsistent information will be discarded, and the extent to which this might have impacted the results will be reported.

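### One pair of tests is named for two kinds of comparison: the chi-square test does not fit paired Q1-Q4 categorical answers, and the signed-rank test does not fit completers versus dropouts

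*Protocol article*

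**What the plan says.** All the relevant text is in the Protocol article under Data Management and Statistical Analysis. The analysis is mainly descriptive, and two uses of statistical tests are mentioned.

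- A check for bias: "comparing data from participants who complete the study with participants who drop out or are excluded". These are different people.
- An optional comparison over time: "Statistical tests might also be used to compare information from the initial questionnaire Q1 and the data from the follow-up questionnaire Q4".

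The sentence that follows names the tests, giving the Wilcoxon signed-rank analysis for a "mean comparison of the quantitative data and the chi-square test for qualitative data". It does not say which of the two comparisons it serves. No paired method for categorical data is named anywhere in the article.

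That Q1 and Q4 are paired follows from the rest of the article. The study is described as "with a longitudinal design and no control group" (Overview). On Q1, Study Procedures and Timeline says: "This questionnaire was available to each participant through a participant-specific link, which was sent by email once they were accepted". Q4 is the "1-year follow-up questionnaire [58]: contained a maximum of 351 questions" (Questionnaires), the same maximum as Q1 and with the same expected average of 50. On the analysis set: "The data analysis will focus on the outcomes of the participants who completed the study".

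**The concern.** The signed-rank test works on within-person differences, so for quantitative items the plan respects the pairing. For qualitative items it names a test that assumes independent observations. There are two ways to apply that test to Q1 and Q4, and neither answers whether answers changed over the year. Stacking the two questionnaires as separate samples discards the within-person correlation, and real change becomes harder to detect. Cross-tabulating Q1 against Q4 asks whether a person's two answers are related, so stable answers alone can give a small p-value that is then misread as change.

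Reading the sentence as meant for completers versus dropouts moves the problem. Chi-square then fits, but a signed-rank test has no pairs to work on. If the sentence is meant for both comparisons, each test is wrong for one of them. At stake are any tests of categorical change over the year, such as employment status or use of a given substance.

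**Working it through.** **Inputs from the article.** Sample Size expects 80 candidates and about 50% loss: 80 × 0.5 = 40 final participants, as stated; 40 × 12 monthly uses = 480 trials, also as stated. Sample Size adds that the number was not derived from any test, so there is no power figure to reproduce. Results reports 17 of 182 candidates with at least one self-administration trial.

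**Assumptions, none given in the article.** Two-sided 0.05; a binary item; within-person correlation ρ of 0.1, 0.3, 0.5 and 0.6; no change means 50% at both times; change means 50% falling to 30%. For that fall ρ cannot exceed (0.30 − 0.15)/√(0.25 × 0.21) ≈ 0.65.

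**Step 1: variance.** With proportion p at both times and n pairs, the true variance of the difference is 2p(1−p)(1−ρ)/n. The independent-samples chi-square uses 2p(1−p)/n, too large by 1/(1−ρ): 1.11, 1.43, 2.0 and 2.5 for the four ρ. Its large-sample rejection rate under no change is 2[1 − Φ(1.96/√(1−ρ))], which gives 1.9% at ρ = 0.3 and 0.6% at ρ = 0.5.

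**Step 2: 40 pairs.** Rejection rates were obtained by summing multinomial probabilities over all possible 2×2 tables (no continuity correction). They agree with simulation.

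| ρ | 0.1 | 0.3 | 0.5 | 0.6 |
|---|---|---|---|---|
| No change: chi-square, independent samples | 4.4% | 2.3% | 0.7% | 0.3% |
| No change: chi-square on Q1 × Q4 table | 9.6% | 47.3% | 90.7% | 98.3% |
| No change: mid-p McNemar | 4.7% | 4.6% | 4.1% | 3.8% |
| 50% to 30%: chi-square, independent samples | 45.5% | 44.8% | 43.5% | 42.3% |
| 50% to 30%: mid-p McNemar | 46.8% | 56.9% | 72.3% | 84.4% |
| 50% to 30%: exact McNemar | 39.2% | 47.8% | 62.7% | 75.1% |

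**Step 3: 17 pairs.** This is only a small-sample scenario, because 17 is not a count of Q4 completers. For the same fall and the same four ρ:

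- chi-square has power 21.8%, 18.7%, 14.7% and 12.4%;
- mid-p McNemar has 19.7%, 22.2%, 24.3% and 24.5%;
- exact McNemar has 12.5%, 13.1%, 12.6% and 11.4%.

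Under no change the cross-table chi-square rejects about 7%, 24%, 57% and 75%.

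**Step 4: two worked tables with 40 people.**

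- *Change.* 20 say yes at Q1 and 28 at Q4, with 1 switch one way and 9 the other. Independent-samples chi-square = 3.33, p = 0.068. McNemar = (1 − 9)²/10 = 6.4, p = 0.011 (exact 0.021).
- *No net change.* Cells 18, 2, 2, 18. Cross-table chi-square = 40 × (18×18 − 2×2)²/20⁴ = 25.6, p ≈ 4 × 10⁻⁷. McNemar = (2 − 2)²/4 = 0.

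**The case against.** The strongest reply is that little depends on this. The Q1-Q4 tests are optional, the analysis is mainly descriptive, and the main outcome is the change in visual analog scale scores from Q3a to Q3b, which this sentence does not affect. None of the three research questions needs a categorical Q1-Q4 test, and descriptive Q1 and Q4 proportions remain correct. All of that stands, and it sets the weight of the point.

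A second reply is that McNemar's test is itself a chi-square test, so the wording may be shorthand, with the exact variant left to a fuller plan. That is possible, and so the text does not prove that a wrong analysis will be run. It does not remove the defect. The article did not leave the choice open: it named a paired variant for quantitative items and only the plain test for qualitative ones, and a statistician following it literally would run the wrong test.

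A third reply concerns size. At ρ = 0.1 the independent-samples chi-square is close to its nominal level and loses almost no power; the large effects need moderate to high correlation. With 17 pairs, mid-p McNemar gains at most about 12 percentage points, and exact McNemar gains nothing. This also stands, which is why a range is shown.

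A reader might infer that every categorical change over the year will be tested wrongly. The article does not support that: it says only that such tests might be run.

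**Conclusion.** The point holds as a defect in a stated rule. One pair of tests is given for a paired and an unpaired comparison, and under any literal reading one of the two does not fit. The consequence is confined to whatever secondary categorical Q1-Q4 tests are carried out or, on the other reading, to the quantitative completer-versus-dropout checks.

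The direction does not depend on the assumed values as long as a person's two answers are positively correlated: the independent-samples chi-square is conservative and the cross-table version flags stability as if it were change. The size does depend on them, from slight at ρ = 0.1 to large at 0.5 and above. The cross-table error is the more serious, because it concerns the hypothesis and no sample size cures it. A stronger reading, that the study's main results are compromised, is not supported. It should be fixed, but it is not critical.

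**What to change.** Split the sentence by comparison.

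- **Q1 versus Q4, same participants:** signed-rank test for quantitative items; McNemar's test (mid-p or exact) for binary items; a marginal-homogeneity test (Stuart-Maxwell or Bowker) for items with more than two categories, collapsing categories or using an exact version where cells are sparse. Report the paired difference in proportions with its confidence interval.
- **Completers versus dropouts or excluded:** rank-sum test for quantitative items; chi-square for qualitative items, or Fisher's exact test when expected counts are small.

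The cost is one rewritten sentence and different function calls in R. No new data are needed, and the article states that the analysis was still under way.

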### Ethical Considerations

This study was approved by the IRB of IMIM on December 11, 2018, after the first submission in October 2018, when clarifications were asked and delivered in November 2018.

The study has been designed and is being executed according to the basic principles of rights and dignity of the human being, as stated in the Helsinki declaration, and this study complies with all the current regulations that apply, including institutional, local, national, and international regulations.

All information is being handled confidentially according to the organic Spanish law 15/1999 and the European regulation 2016/679. The IRB has always granted access to any study information required.

All participants will receive the participant information sheet and will be required to read and fill the IC form, which will be sent to [contact]. The principal investigator will be responsible for reviewing all candidates’ IC forms and screening questionnaires for inclusion and exclusion criteria. All candidates and participants will have the opportunity to ask as many questions as needed before proceeding to any part of the study, both through the forum and through contacting the leading researcher email ([contact]).

Participants will not be required to sign IC forms to protect their anonymity and avoid sharing data that could be used to track their physical identity. The identity that will be protected by the researchers will be the online one, as no other information relatable to the real identities will be given. This procedure is consistent with the methodology of previous studies [61].

The researchers will try their best to limit the influence of their interactions on the participants’ behavior, especially the ones targeted in the study. However, as recommended by previous research, the participants will be involved in discussing the study design and incentivized to share their opinions on how the study could be improved [8,21].

Protocol changes will be communicated to the participants through the online platform once they are approved.

A more extensive ethical analysis by principles can be found in Multimedia Appendix 6 [26,27,39-52,62-64].

### Dissemination Policy

All individual and collective data, as well as all the results derived from the study, will be strictly protected and will only be published with the authorization of the principal investigator and the affected participants. All relevant findings will be sent for publication in suitable journals and submitted for presentation at relevant scientific meetings. The funding organizations will have no role in the publication process. In addition, data without identifiable information will be shared with study participants after assessment and approval by the research team. Finally, all results published in the scientific literature will also be made available in lay language to the communities of origin of the participants. Authorships in the publications will be determined by the amount of scientific and academic contributions of the members of the research team, including external collaborators. There are no plans to make the data sets publicly available.

## Results

The research protocol was approved by the IRB of the *IMIM* on December 11, 2018. Data collection started in August 2019 and was still ongoing when the protocol was submitted (September 2020), finalizing in October 2020.

Data analysis began in November 2020, and it is still ongoing. The authors expect to submit the first manuscript with preliminary results by the end of 2021.

From a total of 182 screened candidates, only 17 (9.3%) completed at least one self-administration trial, resulting in a total number of 64 self-administration trials. From these, 40 different substances were analyzed.

## Discussion

It is possible to conduct an IRB-approved study using this new methodology and collect the expected data. However, the meaning and usefulness of these data are still unknown.

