### Study Objectives and Hypothesis

The study has been designed to answer 3 main research questions:

Who are the people who first try the new substances when they emerge in the market?What are the substances emerging right now and their subjective effects?Is it possible to collect reliable data to answer these questions using a low-budget internet platform and the design used in this study?

The researchers’ initial hypotheses are as follows:

The population of e-psychonauts will be made up of functional and educated people who use drugs mainly in a recreational way.During the study period, we will be able to identify a wide variety of different substances, some of which have never been reported before in the scientific literature or by the organizations aimed at controlling illicit drug supply.The study design and implementation will attract enough research participants with sufficient commitment to provide valuable, reliable, and meaningful data to generate quality evidence.

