### Sample Size

In the most recent review consulted by the authors, the sample sizes reached with web-based questionnaires in people who use illicit drugs ranged from 80 to 9867 [36]. The expected losses while filling these types of questionnaires are about 50% of the sample, but the authors have not found other online longitudinal studies including questionnaires like this one. According to the aforementioned review, the authors expected 80 candidates as the best possible estimate to achieve 40 final participants. Assuming that each participant takes one NPS every month during the duration of the study, the expected number of registered self-administration trials of NPS would be 480. As the study has been designed as exploratory, the sample size could not be determined based on the needs to perform specific statistical tests.

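### The article concludes without qualification that the expected data can be collected, although the reported yield was 64 self-administration trials against 480 expected

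*Protocol article*

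**What the plan says.** Study Objectives and Hypothesis makes feasibility the third of three research questions. The matching hypothesis is: "The study design and implementation will attract enough research participants with sufficient commitment to provide valuable, reliable, and meaningful data".

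Sample Size gives the only numbers against which enough could be judged. It states "The expected losses while filling these types of questionnaires are about 50% of the sample", and then "the authors expected 80 candidates as the best possible estimate to achieve 40 final participants". With one substance per person per month as its premise, it adds that "the expected number of registered self-administration trials of NPS would be 480". The same section calls the study exploratory and says that its size was not derived from any statistical test.

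Results reports: "From a total of 182 screened candidates, only 17 (9.3%) completed at least one self-administration trial". These people produced 64 trials, and 40 different substances were analysed.

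The Discussion then concludes: "It is possible to conduct an IRB-approved study using this new methodology and collect the expected data". The Conclusions paragraph of the abstract repeats this. In both places the next sentence leaves open what the data mean and how useful they are. Neither place compares the yield with Sample Size, and the abstract gives no counts at all.

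**The concern.** Sample Size states the expectation as counts and uses the word expected for them. The conclusion uses the same word and reports success, while the counts printed directly above it in Results fall far short. The caveat that follows concerns interpretation and value. It says nothing about quantity.

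The answer to a main research question is at stake. Whether enough people will commit to a chain of questionnaires, sample submission and repeated reporting is what a methodological pilot of this kind should tell the next team. A reader of the abstract alone would learn that the method delivers what was expected, and would have no figure to set against that.

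**Working it through.** **Inputs**
- Sample Size: 80 candidates, about 50% loss, 40 final participants, one substance per participant per month, 480 trials.
- IRB-Approved Protocol Changes: follow-up per participant was lengthened from 6 months to 1 year by the second amendment.
- Results: 182 screened, 17 with at least one trial, 64 trials.
- Study Setting: laboratory analysis stopped for 3 months.

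**The plan's own figures reproduce**
- Final participants: 80 × (1 − 0.50) = 40.
- Trials: 40 × 1 per month × 12 months = 480.
- Reported percentage: 17 / 182 = 9.3%.

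There is no arithmetic error in the document. The issue is the conclusion drawn from correct figures.

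**Achieved against expected**
- Trials: 64 / 480 = 13.3%, a shortfall of 416.
- People: 17 with at least one trial, against 40 expected final participants (17 / 40 = 42.5%). The two counts are not defined in the same way (see the objection).
- Candidates: 182 against 80. Only this count exceeded expectation.

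**Does the shortfall in trials depend on how the expectation is read?**
- With the earlier 6-month follow-up: 40 × 6 = 240, and 64 / 240 = 26.7%.
- With 9 months, on the assumption that no trial could take place during the laboratory stoppage: 40 × 9 = 360, and 64 / 360 = 17.8%. The assumption is generous to the study, because participants were free to consume without waiting for a result.
- With only the 17 contributors, each followed for 12 months: 17 × 12 = 204, and 64 / 204 = 31.4%.

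The last line gives a further check. At the assumed rate of one per month, 17 people followed for a full year would yield 204 trials, which is 204 / 480 = 42.5% of the expectation. Shorter follow-up among those 17 could therefore explain part of the gap, but not all of it. None of these readings brings the yield to even a third of what was expected.

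**The case against.** The strongest reply is that the phrase about expected data refers to the kind of data: reports of effects matched to laboratory-analysed samples. The Objective and Methods of the abstract describe the product in those terms, and data of that kind were obtained. This stands in part. It makes the sentence ambiguous rather than plainly false. It does not rescue the unqualified wording, because the document also states its expectation in numbers and its third hypothesis is about having enough committed participants.

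Several stronger readings are tempting, and the documents do not support them.

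- **That the third hypothesis has been declared met.** The hypothesis ends in valuable, reliable and meaningful data, and the sentence after the conclusion says that meaning and usefulness are unknown. The article stops short of claiming the hypothesis.
- **That the study failed a feasibility criterion.** The figures 40 and 480 are described as a best estimate and as conditional on an assumption, in an exploratory study that found no comparable longitudinal precedent. They were not success thresholds, and making them benchmarks now would set a criterion after the data are known.
- **That retention was 9.3% against a planned 50%.** The 182 are screened candidates and may include people rejected on eligibility. The 50% is loss while filling in questionnaires. The number accepted is not given, so retention cannot be calculated. Treating the 9.3% as several successive 50% losses would be fitting after the fact, because the number of steps is not derived from the document.
- **That 17 of 40 is the achieved share of final participants.** The 17 have at least one trial. Someone might finish follow-up with no trial, and the number of completers is not reported. As a count of people supplying trials, however, 17 is favourable to the study, since the plan assumed monthly trials from all 40.
- **That 64 / 17 = 3.8 trials per person can be set directly against 12.** Recruitment was sequential, collection ended in October 2020, and the first participant reached one year in August 2020. Later entrants may have been cut short, and person-months are not given.
- **That the plan should have allowed for the laboratory stoppage.** It came with the March 2020 lockdown, after the design was completed in October 2018.

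It is also fair to say that Results discloses the counts openly and that the analysis is called preliminary. But the abstract and Results both give October 2020 as the end of this collection period, although Study Procedures still describes recruitment as ongoing. The counts and the conclusion appear in the same article and should agree.

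**Conclusion.** The point holds as a mismatch between the conclusion and the document's own numeric expectations. The yield was 64 of 480 expected trials (13%), or 27% of the 240 implied by the earlier 6-month follow-up. The trials came from 17 people, against 40 expected final participants. The comparison of trials carries the point. The comparison of people supports it but is not strictly like for like.

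The verdict rests on reading the Sample Size figures as planning expectations, and on treating the reported counts as those of the closed first collection period. It does not show that the design failed, that a threshold was missed, or that the planning figures were miscalculated. What the documents support is narrower: approval was obtained and data of the intended kind were collected online, but feasibility at the planned scale was not shown.

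**What to change.** Reword the Discussion and the abstract's Conclusions to say that approval and online collection of the intended kind of data were possible. Add that the yield was 64 of 480 expected self-administration trials, from 17 people with at least one trial against 40 expected final participants, so that feasibility at the planned scale was not shown.

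Place a short table of achieved against planned counts (candidates, people, trials) beside the conclusion, and give the main counts in the abstract. Label the planned column as planning expectations. Note under the table that 17 and 40 are defined differently and that person-months are not given. If the number accepted, the number of completers and the person-months are available, adding them would allow a proper rate and a proper retention figure.

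The cost is two sentences, one small table, and a conclusion that reads less favourably. Nothing in the design, outcomes or analysis changes.
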